## Abstract

Regardless of the benefits of fall prevention programs, people with Parkinson’s disease (PD) will still fall. Therefore, it is crucial to explore novel therapeutic approaches that are well-accepted and effective for addressing fall risk and the fear of falls among this population. The present study aims to assess the feasibility of the Landing Wise program as a therapeutic intervention for reducing the fear of falling in people with PD. A mixed-methods study will be conducted using convenience sampling to recruit 20 people with PD with a moderate concern of falling from a Parkinson’s Patients Association. In addition to usual care, participants will attend 2 days per week, 90 min group sessions for 8 weeks. The intervention combines group cognitive behavioral intervention with the training of safe landing strategies. Feasibility will be assessed by six key domains (recruitment strategy and rates, enrollment, retention, acceptability, reasons for decline/withdrawal, and adverse events). Quantitative data will be analyzed using descriptive statistics to characterize the sample, followed by inferential statistics to evaluate differences in the Short Falls Efficacy Scale-International Scale, Movement Disorder Society Unified Parkinson’s Disease Rating Scale, Timed Up Go, 6-Minutes Walking Distance, and fall frequency and severity scores between baseline and final assessment. Qualitative data will be analyzed using an inductive thematic analysis process. There is a growing interest in developing new effective therapeutic approaches for people with PD. If proven program feasibility, this study precedes a randomized controlled trial to establish the effectiveness of the Landing Wise program.

## Introduction

1.

Parkinson’s disease (PD) is a chronic degenerative disorder of the central nervous system that primarily affects the motor system, triggering involuntary or uncontrollable movements, like tremors, rigidity, bradykinesia, and difficulty with balance and coordination (1, 2). However, PD can also cause non-motor complications such as cognitive impairment, sleep disorders, mental health disorders, pain, and sensory disturbances (2). In the last two decades, PD prevalence has doubled, and it is estimated that in 2019 affected over 8.5 million individuals (1, 3). Progression of PD symptoms leads to restrictions in many life areas, ultimately resulting in high rates of disability and care requirements (4).

In 2019, the WHO (1) estimated that PD resulted in 329,000 deaths, showing an increase of over 100% in the last two decades, and was responsible for 5.8 million disability-adjusted life years, resulting in a rise of 81% over the same period, escalating faster than for any other neurological disorder worldwide.

Falls are common among people with PD (5, 6), and, notably, the fall rate in this population is often higher than that observed in older adults without PD (5, 7). Consequently, they can experience fearful anticipation of falls, developing a fear of falling (FOF) (8, 9). The FOF can ultimately reduce balance performance and limit the person’s activity levels (8, 10), compromising one’s quality of life (11). Fall prevention programs mainly targeted intrinsic (e.g., muscle weakness, balance problem) or extrinsic (e.g., environmental hazards) fall risk factors (9, 12). Despite the benefits of these programs, it is crucial to highlight that participants within these programs are still at risk of falling (13).

It is vital to develop novel therapeutic approaches that are technically feasible, economically valuable, and culturally, ethically, and socially accepted for addressing fall risk and the FOF among this population (14–16).

Recent studies show that it is possible to reduce the fear of falling among older adults (17, 18). In addition, there is evidence that cognitive behavioral therapy (CBT) can effectively reduce the fear of falling, with significant immediate retention effects for up to 12 months (19–21). CBT is a psychotherapeutic skills-based, non-pharmacological treatment aimed at modifying individuals’ thoughts and behavior by teaching practical strategies to support the individual more effectively in navigating daily challenges (22). In the Landing Wise program context, CBT principles and techniques are seamlessly integrated to address the physical aspects, such as safe landing strategies, and the psychological aspects, including FOF and anxiety, commonly experienced by individuals with PD.

The Landing Wise program takes a comprehensive approach that goes beyond physical training. It delves into the cognitive and emotional dimensions of FOF and anxiety, helping participants explore the intricate connections between their thoughts, feelings, and behaviors. Doing so empowers them with practical strategies to navigate daily challenges more effectively and adjust thought patterns—particularly those marked by negativity or behaviors like social isolation and withdrawal (23).

Previous studies have shown that CBT is a feasible treatment for anxiety and depressive symptoms in people with PD (24–27). More importantly, when applied to address FOF, CBT may yield broader positive outcomes, potentially reducing falls and enhancing overall activities of daily living (28, 29). The versatility of CBT allows for deploying a wide range of strategies can be used in CBT, such as cognitive restructuring, training of coping skills, or practicing new skills that can be used in real-world situations to help people with PD to overcome these patterns. For instance, as part of the Landing Wise program’s integration of CBT, individuals grappling with FOF may actively practice safe landing strategies. Not only do these strategies provide tools for safe fall management, but they also reduce the impact load of a fall. A systematic review by Moon and Sosnoff (13) synthesized findings from 13 studies on safe landing strategies, demonstrating their potential to reduce the risk of injury during falls significantly. The authors concluded that landing strategies significantly decrease the impact load during a fall and might effectively reduce the impact load of falling.

Considering that previous studies have shown the positive effects of CBT and practice safe landing strategies on people at risk of falling, here, we combine the two approaches in a program. Therefore, in this study, our primary aim is to assess the feasibility of the Landing Wise program as a therapeutic intervention for reducing FOF in people with PD. Secondary objectives include assessing the program’s preliminary effects on the people with PD.

## Materials and methods

2.

### Study design

2.1.

This study is a mixed methods study using quantitative and qualitative assessments. To ensure the quality of the research protocol report, we will use The Good Reporting of A Mixed Methods Study (GRAMMS) checklist (30).

### Study setting

2.2.

The intervention will be delivered in a gymnasium of a Day Care Unit from a Private Institution of Social Solidarity in the region of Lisbon and Tagus Valey in Portugal that caters to a population of over 80,000 people.

### Sampling and recruitment

2.3.

The study population consists of people with PD recruited from the Parkinson Patients Association and the outpatient neurology units from two hospital centers in Lisbon and Tagus Valley. The sampling method selection will be non-probabilistic by convenience. All eligible candidates will be invited to join the program.

Participants will be included if they fulfill the inclusion criteria:

Diagnosis of idiopathic PD (Movement Disorder Society PD criteria) (31);Hoehn and Yahr stages II–IV (32);Age above 18;Moderate concern of falling with the Short Falls Efficacy Scale International (Short FES-I) >9 (33);A Montreal Cognitive Assessment (MoCA) score > 25 (Normal cognition) (34);Able to tolerate a minimum of 45 min of exercise (Following recommendations form PD guidelines) (35);Able to communicate with the investigator, to understand and comply with the study procedures;Willing and able to provide written informed consent to participate and understand the right to withdraw their consent at any time without prejudice to future medical care.

Participants will be excluded if they have any of the following:

A MDS-UDPRS Part III item 3.12 score > 3 (Severe postural instability: very unstable, tends to lose balance spontaneously or with just a gentle pull on the shoulders);Severe cognitive difficulties and significant active psychiatric problems that aggravate when exercising;Severe hearing or visual impairment;Missed two consecutive sessions.

Our study aims to recruit 20 participants in total. This sample size was calculated using G*Power (36), taking into account a large effect size (dz = 0.8), an alpha level (α) of 0.05, and a statistical power (1-β) of 0.8. These calculations were performed for both the two-tailed matched pairs t-test and the two-tailed matched pairs Wilcoxon signed-rank test, which will be employed in the quantitative data analysis. Further details about these analyses are provided in the data analysis section below. Both tests indicated a required sample size of 15 participants. To account for a possible dropout rate of 25%, we increased the sample size to 20 participants.

In the first stage of recruitment, healthcare professionals (nurses, physiotherapists, and physicians) will be responsible for screening and identifying suitable participants based on the data in the patient’s clinical file (diagnosis, staging of the functional disability associated with PD, and clinical data). These professionals will introduce the study to potential participants and provide an information sheet containing the study aims and procedures. A research team member will contact potential participants who have applied for the recruitment process via telephone to present comprehensive information regarding the study procedures and verify their willingness to participate. We recommend taking a minimum of 24 h to consider the advantages and disadvantages of participating in the study and formulate questions before deciding on participating. Once all questions have been answered, potential participants will be asked to sign an informed consent. Access to patient clinical data will only be granted to the researcher at this stage. Figure 1 shows a flow diagram for participants.

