### Intervention

2.4.

The intervention consists of an 8-week program with 90-min group sessions held twice a week. The program combines group CBT with training in safe landing strategies, thus ensuring each component receives dedicated 45-min sessions (35, 37, 38). This intervention will supplement the usual care.

The intervention will be delivered by a rehabilitation nurse with PhDs in Nursing Sciences and Psychology, trained in Cognitive behavioral therapy, and experienced in motor and cognitive exercise programs. Following European Parkinson’s guidelines (35), we will consider eight people with PD as the optimum number of participants per group.

Assistance to the instructor will be provided by two nurses that are receiving their master’s training in rehabilitation nursing. In addition, the students will receive 8 h of CBT training conducted by a cognitive-behavioral therapist.

To keep the program challenging and engaging, the instructor will gradually raise the complexity of the exercise session accordingly to the participants’ willingness and improved condition. The instructor will use the Borg Effort Perception Scale to assess the participants’ perceived effort through sessions (39). Participants can achieve an intensity rating between 14 (Somewhat Hard) and 17 (Very Hard) on a 20-point Borg scale, indicating a range from somewhat challenging to very hard perceived exertion during exercise (40).

The CBT will be based on the FOF management model (41) that illustrates how community-dwelling older adults think, feel, and act when facing FOF. According to this model, the FOF arises when the person believes falling is an inevitable part of aging. These misconceptions may lead older adults to withdraw from social activities instead of focusing on strategies to manage the problem. The FOF model indicates that older adults may embrace different strategies: display psychosomatic symptoms, adopt an attitude of risk prevention, pay attention to environmental safety, and modify their own’s behavior. The FOF will be relieved when the person is satisfied with the outcomes (41).

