### Data collection

2.5.

Researchers defined the feasibility of trial design and procedures by six key domains for a subsequent registered randomized controlled trial. These key domains will be our primary outcomes and include:

Recruitment strategy and rates (candidates screened, eligible, approached, consented, and excluded after screening).Enrollment (number of participants that attended the program).Retention (percentage of enrolled participants who completed final program assessments).Acceptability (assessed with an *ad hoc* survey and semi-structured exit interviews). The exit survey will consist of Likert scale questions to evaluate the participants’ satisfaction. The interviews aim to gain insight into participants’ perspectives on the intervention’s feasibility, acceptability, and usefulness and identify barriers and facilitators that may influence people with PD to participate in the program.Reasons for decline/withdrawal (the researchers will keep a record of reasons for decline/withdrawal).Adverse events (number of events involving injury).

A qualified research team member will collect secondary outcomes to identify an appropriate outcome and estimate parameters for a sample size calculation for a randomized controlled trial. These assessments will be performed in the week before (T0) and after completing the training program (T1) using the following instruments:

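### Missing two consecutive sessions is listed as an exclusion criterion, so the study itself removes non-attenders and confounds its own retention, acceptability and pre-post results

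*Protocol article*

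**What the plan says.** In Sampling and recruitment, the list introduced by "Participants will be excluded if they have any of the following" closes with "Missed two consecutive sessions". The other items on that list (postural instability, cognitive or psychiatric problems, hearing or vision) can be judged at screening.

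The Intervention section sets the schedule: "The intervention consists of an 8-week program with 90-min group sessions held twice a week". Consent is signed at the end of recruitment, before any session.

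Data collection names six feasibility domains as primary outcomes. Enrollment is the number who attended the program. Retention is the "percentage of enrolled participants who completed final program assessments". Acceptability comes from an exit survey and exit interviews. Reasons for decline or withdrawal are recorded, and injuries are counted. Secondary outcomes are measured "in the week before (T0) and after completing the training program (T1") and are meant to supply parameters for the sample size of the later randomized trial.

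On size, "Our study aims to recruit 20 participants in total": 15 evaluable plus an allowance for 25% dropout.

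**The concern.** A participant cannot have missed a session before joining the program, so this item cannot screen anyone. As written, it removes people already enrolled because they did not attend. Attendance and staying in are part of what a feasibility study is meant to observe, and a rule that ends participation for non-attendance partly determines those results.

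Three results are exposed:

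- **Retention.** The reader cannot tell how much of the loss was imposed by the study and how much was chosen by participants.
- **Acceptability.** The interviews are meant to identify barriers, and people who stopped coming know these best. The Discussion accepts that the landing training may intimidate some people who fear falling, so absence may be related to the outcome.
- **Pre-post change.** If removed participants are not reassessed, the estimate carried into the randomized trial describes regular attenders.

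The Discussion says the results will decide whether a full trial is feasible, so these figures will be acted on.

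**Working it through.** **1. The plan's own figures.** Inputs from Sampling and recruitment: "taking into account a large effect size (dz = 0.8), an alpha level (α) of 0.05, and a statistical power (1-β) of 0.8", two-tailed paired tests. Exact noncentral-t power for the paired t-test is 0.790 at n = 14 and 0.821 at n = 15. For the Wilcoxon test, with effective n = n × 3/π (normal parent), power at n = 15 is 0.801. Then 15/(1 − 0.25) = 20. Both stated figures reproduce.

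**2. What triggers the rule.** Sessions: 8 weeks × 2 = 16. One week away is 2/16 = 12.5% of sessions and triggers exclusion. Missing every other session is 8/16 = 50% and never does. The rule is therefore a poor measure of adherence.

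**3. Retention under the two readings** (20 start, no other loss):

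| Removed | Kept in denominator | Taken out of denominator |
|---|---|---|
| 2 | 18/20 = 90% | 18/18 = 100% |
| 4 | 16/20 = 80% | 16/16 = 100% |
| 5 | 15/20 = 75% | 15/15 = 100% |

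**4. How often the rule might apply.** The article gives no attendance rate. Assume each session is missed independently with probability q. The number of ways to place m non-adjacent misses among 16 sessions is C(17 − m, m), so

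P(removed) = 1 − Σ C(17 − m, m) q^m (1 − q)^(16 − m), for m = 0 to 8.

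Expected removals are 20 × P. The last column is the binomial chance of 6 or more removals, which leaves fewer than 15.

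| Miss rate q | P(removed) | Expected of 20 | Chance of 6 or more |
|---|---|---|---|
| 5% | 3.5% | 0.7 | under 0.1% |
| 10% | 13.0% | 2.6 | 3.7% |
| 15% | 26.2% | 5.2 | 43% |
| 20% | 41.1% | 8.2 | 89% |

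The dropout allowance is 20 − 15 = 5 people. If removed participants have no final assessment, 8 removals leave 12 pairs, and power at dz = 0.8 is 0.714.

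**5. Possible effect on the change estimate** (assumed values, SD of change held constant). Suppose 15 attenders have dz = 0.8 and 5 removed participants have dz = d. The all-enrolled value is (15 × 0.8 + 5d)/20. With d = 0 it is 0.60; with d = 0.4 it is 0.70. For 80% power these need 24 and 19 pairs, against 15 at dz = 0.8.

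**The case against.** **Retention need not be inflated.** A reader might infer that the rule makes retention look better. The definitions in Data collection do not support that as the primary reading: someone who attended is enrolled, and if later removed counts as a non-completer, which lowers retention. This stands. What remains is that imposed and voluntary loss are mixed, and that calling these people excluded leaves room for the other reading.

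**Loss of the final assessment is inferred.** The T1 wording can describe when the program ends rather than a condition on each participant. Nothing says removed participants are not reassessed or interviewed. This also stands: the loss is probable, given that they are excluded, but it is not stated.

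**Adverse events.** A reader might infer that injuries among removed participants are dropped. No such rule appears, and an injury in a session would be counted before any later absence. Incomplete follow-up is a risk only.

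**Mitigation.** Reasons for withdrawal are a primary domain, so absence through injury, fatigue or fear may be captured there. That helps in part but supplies no final assessment and no acceptability data.

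**Size.** The removal counts depend on assumed miss rates. People who withdraw stop attending and would meet the rule anyway, so the two losses overlap and the 25% allowance may already cover both. It would be wrong to say that the rule exhausts the allowance before any withdrawal. Nor does clustering always raise the loss: if absences concentrate in some participants (beta-distributed miss rates, intraclass correlation 0.3), the chance at a 20% miss rate falls from 41% to 35%. Power is secondary here, since the Discussion says effectiveness will not be established.

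**Condensed source.** The flow diagram is not shown, and the full protocol may describe follow-up of removed participants. That weakens the follow-up claims, but not the point that the criterion is misplaced.

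**Conclusion.** The concern holds in a limited form. A post-enrolment event stands among the exclusion criteria and acts as removal for non-attendance, in a study whose primary outcomes include retention, acceptability and reasons for withdrawal. That conflict is in the text and does not depend on any attendance rate.

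Its consequences differ in certainty. The mixing of imposed and voluntary loss follows from the literal definitions. Inflated retention (75% against 100% with 5 removed) arises only if excluded people leave the denominator. Restriction of exit data and pre-post change to regular attenders is probable, with a probable but unproven favourable direction. Incomplete adverse-event follow-up is a risk.

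The number affected is illustrative: from under 1 to about 8 of 20 for miss rates of 5% to 20%, assuming independent absences and overlapping with ordinary drop-out. The sample-size arithmetic is not at fault.

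**What to change.** - Delete the item from the exclusion criteria. Record two consecutive missed sessions, with the reason, as an attendance outcome.
- Keep everyone who started in the feasibility denominators and in the adverse-event count.
- Seek the T1 assessment, exit survey and exit interview from all of them, whatever their attendance.
- Analyse pre-post change in everyone with T0 and T1, with regular attenders as a sensitivity analysis.
- If a rule for stopping session attendance is intended, state it separately and reconcile it with the retention definition. Whether a participant continues sessions is for the investigators.

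The stated 15 and 20 need no change. The cost is protocol wording, a few extra contacts with non-attenders, and possibly less favourable reported figures.

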**Figure 1 fig1:**
[figure not shown]
Flow diagram.

### Intervention

2.4.

The intervention consists of an 8-week program with 90-min group sessions held twice a week. The program combines group CBT with training in safe landing strategies, thus ensuring each component receives dedicated 45-min sessions (35, 37, 38). This intervention will supplement the usual care.

The intervention will be delivered by a rehabilitation nurse with PhDs in Nursing Sciences and Psychology, trained in Cognitive behavioral therapy, and experienced in motor and cognitive exercise programs. Following European Parkinson’s guidelines (35), we will consider eight people with PD as the optimum number of participants per group.

Assistance to the instructor will be provided by two nurses that are receiving their master’s training in rehabilitation nursing. In addition, the students will receive 8 h of CBT training conducted by a cognitive-behavioral therapist.

To keep the program challenging and engaging, the instructor will gradually raise the complexity of the exercise session accordingly to the participants’ willingness and improved condition. The instructor will use the Borg Effort Perception Scale to assess the participants’ perceived effort through sessions (39). Participants can achieve an intensity rating between 14 (Somewhat Hard) and 17 (Very Hard) on a 20-point Borg scale, indicating a range from somewhat challenging to very hard perceived exertion during exercise (40).

The CBT will be based on the FOF management model (41) that illustrates how community-dwelling older adults think, feel, and act when facing FOF. According to this model, the FOF arises when the person believes falling is an inevitable part of aging. These misconceptions may lead older adults to withdraw from social activities instead of focusing on strategies to manage the problem. The FOF model indicates that older adults may embrace different strategies: display psychosomatic symptoms, adopt an attitude of risk prevention, pay attention to environmental safety, and modify their own’s behavior. The FOF will be relieved when the person is satisfied with the outcomes (41).

The program syllabus will be designed based on prior research (42, 43), aiming to restructure misconceptions to foster a positive view of fall risk management, increase self-confidence and physical wellness concerning falling, and a sense of control over falling. The sessions will cover the following themes: (1) introduction; (2) associations with falls and fear of falling; (3) participant’s view of FOF; (4) cognitive restructuring; (5) strategies to manage fall risk; (6) strategies to manage FOF; (7) application of strategies in daily life; and (8) problem-solving (learning how to fall, stand up and call for help).

Each session will be carefully planned by a team composed of a cognitive-behavioral therapist, a rehabilitation nurse, a physiotherapist, and an exercise physiologist, experts in PD, who will develop a guide to help manage each session. Then, a panel of experts in CBT will assess the guide’s appropriateness and contents. The structure of the CBT sessions is described in Table 1.

**Table 1 tab1:** Structure of the CBT sessions.

Phase 1: Warm-Up (5 min)	Social interaction (e.g., greeting friends). Setting a positive and supportive tone for the session. Introduction to the session’s topic. Brief review of the previous session (if applicable). Engaging in a warm-up activity to promote relaxation and focus.
Phase 2: Cognitive restructuring approach (20 min)	Explanation of the concept being addressed. Discussion, group exercises, or role-playing related to the skill. Identifying and addressing cognitive and emotional aspects (e.g., fear of falling, negative thought patterns).
Phase 3: Sharing and Support (15 min)	Encouraging participants to share their experiences or insights related to the session’s topic. Providing support and feedback within the group setting.
Phase 4: Closing (5 min)	Summary of the key points covered in the session. Homework assignments or practice exercises for participants to work on until the next session. Ending the session on a positive and motivating note.

After completing the CBT, the initial stage of safe landing training commences with a 10-min physical warm-up session aimed at reducing the risk of injury. This is followed by a 10-min improvisation phase, wherein participants will have the freedom to move in accordance with specific instructions (such as bilateral movements, large and big movements, movements that are not usually carried out in everyday life activities, as getting up and down from the floor, etc.).

All participants will be equipped with protective gear for the second stage, including a wrist guard and neck protector. The intervention methods consist of 20 min of safe landing training exercises aiming to teach participants how to fall in such a manner to alleviate the impact severity and minimize the risk of injury.

We have chosen the three safe landing techniques that have proven to be effective in reducing the impact severity of various falls (13) (Figure 2), namely:

Backward squatting (flex the knees and hips while contracting the muscles spanning these joints);Forward elbow flexion (catch the ground with the outstretched arms while landing with the slightly flexed elbow);Side forward rotation (rotate forward during the descent to land on the outstretched hands).

